#### **Summary of preclinical studies:**

##### **Efficacy:**

① **Effect of long-acting ropivacaine injection on postoperative pain in rats:** when the dosage was 12mg/mouse, the analgesia of ropivacaine hydrochloride injection lasted for 4h, and 50% of animals died, 50% of animals responded to general anesthesia, which recovered within 2h; The analgesic duration of long-acting ropivacaine injection was 10h. ② **The blocking effect of long-acting ropivacaine injection on nerve conduction in anesthetized rabbits:** In ropivacaine mesylate injection group, local nerve conduction was almost completely inhibited about 5min after administration, and the effect lasted for 2~3h; Long-acting ropivacaine injection group 1(0.89mg/rat), normal saline group and blank solvent group had no effect. Long-acting

ropivacaine injection group 2(3mg/ rat) had a slower effect, and the inhibition duration of nerve impulse conduction was 12-16h. Compared with ropivacaine mesylate group, the sensory nerve block time was 6-7 times longer when the dose of long-acting ropivacaine injection was increased by 3.4 times, and the long-acting ropivacaine injection had a good sustained release effect. ③**The effects of long-acting ropivaine injection on the duration and latency of epidural anesthesia were as follows:** The duration of lower limb paralysis of ropivaine mesylate injection in control group was 4.6, 14.6 and 29.5min when rats were given equal doses (60, 180 and 600  $\mu$  g/ rat); The duration of lower limb paralysis in long-acting ropivacaine injection group was 15.4, 53.3 and 237.2min, respectively. Compared with the control group, the duration of epidural anesthesia in the long-acting ropivacaine injection group was 3.3, 3.6 and 8.1 times, and the long-acting ropivacaine injection significantly prolonged the effect of epidural anesthesia.

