## Pharmacodynamics methods:

**Experimental design, (1) Analgesic range measurement (Experiment 1) :** After the single point of administration, pain points were determined in two directions (when the VAS value of the test point (n) 1cm away from the point of administration was  $\geq 4$ , The measurement can be terminated at (n+1) time point) at 15min, 30min, 45min $\pm$ 3min, 1h, 1.5h, 2h, 3h, 4h, 5h, 6h, 7h, 8h, 9h, 10h, 11h, 12h  $\pm$ 5min, respectively. The distance between pain point and drug administration point (R1, R2) was measured and recorded, and the analgesic range diameter D = (R1 + R2).

**(2) Analgesic maintenance time, onset time and acupuncture pain intensity were measured (Test 2):** the intensity of acupuncture pain was measured before and after 15min, 1h, 4h, 8h, 10h, 12h, 14h, 18h, 21h, 24h, 27h, 30h, 33h, 36h, 48h, 72h;

**Baseline pain measurement:** Before drug administration, visual analogue scale (VAS) was used to measure the pain pressure baseline value (g) of VAS=4,5,6 in the pain test area, repeated for 3 times, and average value was taken respectively, namely the baseline value;

**Acupuncture pain intensity measurement:** a baseline value of VAS=4 was applied to the blank area to remind subjects of the sensation; In the pain test area, the baseline VAS=4 pressure was applied to the area, and the subjects were asked to compare the feeling with the blank area, and the feeling was "weaker", "similar", "stronger"?

When it was "weaker", baseline pressure at VAS= 5,6 was successively given and the inquiry process was repeated. When VAS=6 pressure was applied, subjects felt weaker and did not continue to increase the pressure. When it was "similar", record the maximum pressure value applied at this time; When it was stronger, the maximum pressure of the previous application was recorded and the onset time of analgesia maintenance time and the intensity of acupuncture pain were counted.

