#### **Pharmacodynamics:**

- (1) Maintenance time of analgesia, onset time and intensity of acupuncture pain were measured: the intensity of acupuncture pain was measured before and after administration at 15min, 1h, 4h, 8h, 10h, 12h, 14h, 21h, 24h, 27h, 30h, 33h, 36h, 48h and 72h.
- (2) Analgesic range measurement: 15min, 30min, 45min, 1h, 1.5h, 2h, 3h, 4h, 5h, 6h, 7h, 8h, 9h, 10h, 11h, and 12h after single point administration, analgesic range was measured in two directions (study 1).

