### **Pharmacodynamics index evaluation**

#### **Analgesic onset time:**

**Evaluation of analgesic onset time:** analgesic onset time was recorded as the time when the threshold of measured pain sensation was greater than the threshold of baseline pain sensation of the subject (i.e., baseline

VAS=4 average acupuncture pressure) when the pain sensation was measured after drug administration.

**Pain threshold:** the minimum stimulus intensity when the human body feels pain. Pain threshold usually refers to a stimulus intensity that can cause pain sensation in human body, which is generally divided into pain sensation threshold and pain tolerance threshold (the maximum stimulus intensity that human body can tolerate) .

**Duration of analgesia:** Effective analgesia refers to the pain threshold greater than the baseline pain threshold during pain measurement. Theoretically, the duration of analgesia is the difference between the effective start time and the effective end time of analgesia. However, in the actual operation of this study, real-time dynamic monitoring could not be achieved, so the duration of analgesia in this study was divided into minimum duration of analgesia and maximum duration of analgesia. The true value of analgesic duration was between the minimum duration and the maximum duration.

Minimum duration of analgesia = last time from measurement to effective analgesia - first time from measurement to effective analgesia

Maximum duration of analgesia = (last measured to effective analgesia +1) measurement time - first measured to effective analgesia time

**Table 3: Acupuncture pain intensity: The intensity of acupuncture pain in this study was divided into 3 levels as described in the table below:**

|              |                                                                                                                          |
|--------------|--------------------------------------------------------------------------------------------------------------------------|
| Three Grade  | Pain threshold was measured $\geq$ baseline VAS=6 acupuncture pressure                                                   |
| Second Grade | Baseline VAS=6 acupuncture pressure > threshold of pain sensation $\geq$ baseline VAS=5 acupuncture pressure             |
| First Grade  | Baseline VAS=5 acupuncture pressure value > threshold of pain sensation $\geq$ baseline VAS=4 acupuncture pressure value |

Analgesic range of injection site (Study 1);

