### **Pharmacodynamics analysis**

Pharmacodynamics indexes were described by mean, standard deviation, maximum, minimum and median, and compared with the basic value in screening period. Paired T test was used to compare the differences before and after treatment in groups.

The groups were compared using a least square mean of the difference from baseline (with baseline as a covariable) and a 95% confidence interval.

The mixed effect model was used to analyze the change of acupuncture pain intensity at different time points after

administration compared with that before administration. The model took the change value of pain intensity at different time points in different administration areas compared with baseline as the dependent variable, and the pain intensity before administration as the covariable. Group (experimental group, control group), administration area/blank area, visit site, and interaction between group and visit site were fixed effects and individual factors were considered.

According to the model, the mean value of change in pain intensity at different time points of administration from baseline and its 95% confidence interval were calculated, as well as the mean value of difference between the experimental group and the control group and its 95% confidence interval.

Similar methods were used to analyze the range of analgesia.

Kaplan-meier method was used to statistically analyze the onset time and maintenance time of analgesia, and the median, Q1, Q3 and 95% confidence interval of the onset time and maintenance time of analgesia were calculated.

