- 9) The coagulation function test included prothrombin time (PT), activated partial thrombin time (APTT), thrombin time (TT) and fibrinogen content (FIB). Check once during screening period.
- 10) Women must have a blood pregnancy test at screening and on day 4.
- 11) Routine urine examination should include glucose (GLU), ketone body (KET), protein (PRO), urinary occult blood (BLD), white blood cell (WBC), bilirubin (BIL), nitrite (NIT), pH, urochologen (UBG), specific gravity (SG); The screening period and the fourth day were examined once.
- 12) Pain test: measure the mechanical pressure value applied vertically when VAS=4.
- 13) Alcohol breath test and drug abuse screening (including morphine, methamphetamine, ketamine, methylene dioxy-amphetamine, THC) should be performed once a day.
- 14) 12-lead electrocardiogram was examined once during screening period, once on day -1 and once on day 4.
- 15) When necessary.
- 16) Collect drug combination data, including drug dose, route of administration, administration schedule, start date, indication, and end date, and record the data from the beginning of the trial until the end of follow-up.
- 17) After screening, subjects should be asked whether they suffer from acute diseases; Have you taken any alcohol-based products in the 24 hours prior to study administration; Whether you exercise vigorously; Whether to maintain a good living condition; Drink (or consume) theophylline, caffeine, theobromine, and alcohols 48 hours before administration of the study drug.
- 18) Collection of blood pharmacokinetic samples: Blood pharmacokinetic samples were collected at 0.5h, 1h, 1.5h, 2h( $\pm 2$ min), 4h, 6h, 8h, 10h, 12h, 21h, 24h, 27h, 30h, 33h, 36h, 48h and 72h( $\pm 5$ min) after 15min before administration.

- 19) Acupuncture pain intensity was measured before and after administration at 15min, 1h, 4h, 8h, 10h, 12h, 14h, 21h, 24h, 27h, 30h, 33h, 36h, 48h and 72h (the time window of measurement point from 15min to 72h was  $\pm 15$ min).
- 20) Local skin irritation at the injection site: scores were scored before and after administration 20min, 40min, 1h, 2h, 6h, 24h, 48h and 72h (the time window from 20min to 1h observation point was  $\pm 3$ min; The observation time window from 2h to 72h is  $\pm 5$ min).
- 21) When subjects withdraw from the study, they should be checked as far as possible according to the safety evaluation on the fourth day after the end of drug administration to complete the withdrawal visit.

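### Test 2 analgesic onset is taken as the first positive reading on a sparse early grid and summarised by Kaplan-Meier with no lower bound, so it is shifted late by up to the width of the gap

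*Protocol*

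**What the plan says.** All references are to the Protocol.

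- **Recording rule** (*Pharmacodynamics index evaluation*, first entry), which reads: "analgesic onset time was recorded as the time when the threshold of measured pain sensation was greater than the threshold of baseline pain sensation". This is judged when pain is measured, so onset is the time of the first positive reading.
- **Reading times, Test 2** (*Pharmacodynamics methods*): "the intensity of acupuncture pain was measured before and after 15min, 1h, 4h, 8h, 10h, 12h, 14h, 18h, 21h". The *Pharmacodynamics* paragraph under *Observation indicators* repeats the list: "the intensity of acupuncture pain was measured before and after administration at 15min, 1h, 4h, 8h, 10h, 12h, 14h, 21h, 24h". The two lists differ at 18 h but agree on every early time. Note 19 to Table 10 has the same early times, and "the time window of measurement point from 15min to 72h was" ±15 min.
- **Analysis** (*Pharmacodynamics analysis*): "Kaplan-meier method was used to statistically analyze the onset time and maintenance time of analgesia". No method for interval-censored times is named. The planned summaries are given as follows: "the median, Q1, Q3 and 95% confidence interval of the onset time and maintenance time of analgesia were calculated".
- **Duration, for contrast** (*Pharmacodynamics index evaluation*): the Protocol says that continuous monitoring is not feasible and reports a minimum and a maximum duration. Onset has no such bounds.
- **Role of onset**: it belongs to the second secondary objective. It is also a secondary indicator to be compared between the test and positive control groups (*Observation indicators*).

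**The concern.** A first positive reading at 4 h shows only that analgesia began after the 1 h reading and by the 4 h reading. Recording 4 h and passing it to Kaplan-Meier treats the upper end of that interval as the event time. The median and quartiles then move to the upper ends of the gaps. The confidence interval reflects variation between subjects but not the width of the gap, so the result looks more exact than the data allow.

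The shift need not be equal in the two groups, because the gaps widen from 15 min to 4 h over the first 8 h. If the control acts within the first gap and the long-acting product acts in a later one, the recorded difference in onset includes a part that comes from the reading schedule. The preclinical summary hints at this. With the aqueous mesylate salt in anesthetized rabbits, "local nerve conduction was almost completely inhibited about 5min after administration", while the long-acting product acted more slowly. That is a different salt, species and measure, so it shows only that unequal shifts are possible.

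**Working it through.** The Protocol states no onset figure, so there is none to reproduce.

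**Inputs.** Early Test 2 reading times (*Pharmacodynamics methods*): 0.25, 1, 4, 8, 10 h. Recording rule: first reading above baseline. Reading window: ±0.25 h (Table 10, note 19). Group sizes (Table 1): 6 test and 3 control subjects in cohort A, 8 in each of cohorts B to E.

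**Step 1: largest shift, with no distributional assumption.** For true onset in (a, b], the recorded value is b and the shift is below b − a.

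| True onset lies in (h) | Recorded (h) | Largest shift (h) |
|---|---|---|
| (0, 0.25] | 0.25 | 0.25 − 0 = 0.25 |
| (0.25, 1] | 1 | 1 − 0.25 = 0.75 |
| (1, 4] | 4 | 4 − 1 = 3 |
| (4, 8] | 8 | 8 − 4 = 4 |
| (8, 10] | 10 | 10 − 8 = 2 |

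These are nominal times. If the earlier reading is 0.25 h early and the later one 0.25 h late, the two widest gaps become 4.25 − 0.75 = 3.5 h and 8.25 − 3.75 = 4.5 h.

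**Step 2: typical shift, under an assumption.** The documents give no human onset distribution. Assume a log-normal onset with log-SD 0.4 or 0.5, vary the true median, and move each simulated onset up to the next reading time.

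| True median (h) | Recorded median (h) | Shift of median (h) | Mean shift per subject (h), log-SD 0.4 / 0.5 |
|---|---|---|---|
| 0.1 | 0.25 | 0.15 | 0.15 / 0.16 |
| 0.5 | 1 | 0.5 | 0.55 / 0.62 |
| 1.5 | 4 | 2.5 | 1.94 / 1.77 |
| 2 | 4 | 2 | 1.87 / 1.82 |
| 3 | 4 | 1 | 1.70 / 1.77 |
| 5 | 8 | 3 | 1.80 / 1.72 |

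Rounding up keeps the order of the onsets, so in a large sample the recorded median is the upper end of the gap that holds the true median. The second and third columns therefore do not depend on the log-normal shape; the last column does. For true medians of 1.5 and 2 h, the recorded first quartile, median and third quartile are all 4 h.

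**Step 3: at the trial's group size.** In 20,000 simulated groups of 8 (log-SD 0.4), the Kaplan-Meier median of recorded onset exceeded that of true onset on average by 0.15, 0.52, 2.50, 2.09, 1.22 and 2.52 h for the six true medians above. Small groups do not remove the shift.

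**Step 4: what an interval analysis gives.** A recorded 4 h becomes 1 to 4 h, and a recorded 8 h becomes 4 to 8 h. The lower end is the previous reading, which is already collected.

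**The case against.** **On a shared grid the estimator changes little.** If every subject is read at the same nominal times with none missing, the Turnbull estimate puts on each interval the mass that Kaplan-Meier puts on its right end. The two curves agree at every reading time. This stands: the gain lies mainly in reporting a range instead of a point. It still changes the stated result, and with actual reading times inside a ±15 min window the grids are no longer identical.

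**It could be left to the SAP.** An SAP may exist and may name an interval-censored method. But the Protocol itself fixes both the recording rule and Kaplan-Meier, so the wording needs correcting there.

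**Onset is secondary, and the groups are small.** This stands as a limit on importance. The analysis section plans medians, quartiles and intervals for onset, with no test, and no estimator makes a comparison with 3 controls precise.

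Some stronger statements are tempting, and the documents do not support them:

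- *That median onset will be overstated by 3 to 4 h.* This is the worst case, for onset just after 1 h or 4 h. If onset falls within the first hour the limit is 0.25 to 0.75 h.
- *That recorded onset is always late.* If nominal times are used, a 15 min reading taken at 28 min would record a true onset of 20 min as early. No confirming reading is required either, so one chance response could set onset too early.
- *That the median can only be a reading time.* Software that averages two event times when the curve sits at 0.5 returned a midpoint in up to 31% of simulated groups of 6 or 8.
- *That every control subject would be recorded at 15 min.* This carries a rabbit nerve-conduction result with the mesylate salt over to subcutaneous ropivacaine hydrochloride in volunteers, tested at points 1, 3 and 4 cm from the circle centre.

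**Conclusion.** The point holds as a low-cost improvement in how onset is defined and reported. Followed as written, the plan gives onset times that, apart from the reading window, are late by at most 0.25, 0.75, 3 or 4 h according to the gap in which true onset falls. These limits follow from the schedule alone. The mean shifts of about 0.5-0.6 h (true median 0.5 h) and 1.7-1.9 h (true medians 1.5-5 h) rest on the assumed log-normal onset with log-SD 0.4 to 0.5. True medians of 1.5, 2 and 3 h cannot be told apart by the recorded median.

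Which gap applies to either product in humans is unknown from the documents. A shift that differs between test drug and control is therefore a possibility, not an established bias.

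**What to change.** 1. In *Pharmacodynamics index evaluation*, define Test 2 onset as the interval (last ineffective reading, first effective reading], using actual reading times. Where the first reading is already effective, use (0, first reading]. Report earliest and latest onset for each subject.
2. In *Pharmacodynamics analysis*, replace Kaplan-Meier on the first positive reading with the Turnbull (interval-censored) estimate, and give the median and quartiles with their interval limits.

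**Cost.** A wording change on data already collected, with no extra readings. The downside is that the median appears as a range, such as 1 to 4 h, where readings are sparse.

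**Not recommended.** Moving late readings into the first hours would widen the late intervals that determine duration, a central outcome for a long-acting product. A Weibull interval-censored model would ask more of groups of 3 to 8 subjects than they can support.

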### **Processing of missing data**

Processing of missing data from safety, pharmacokinetic and pharmacodynamic analyses was not considered in this study.

### **Research on management**

**Inspection:** in order to ensure the clinical trial participants' safety and rights guaranteed, test record and report the data is accurate, complete and correct, and ensure the test follow the approved plan and the relevant laws and regulations, the bid will be specified with proper qualifications of clinical arbitrator as main contact between the sponsor and the researchers, in the study of the center for inspection. During the study, the investigator should allow sponsor inspectors or representatives to visit the study facility to review documents related to the study (e.g., subject informed consent, drug inventory, and IRB approval documents).

When the examiner visits, the subject's files will be rigorously reviewed to verify that the information recorded in the case report form or eCRF, especially the key information related to safety, matches the subject's original records.

Monitoring activities should follow standard operating procedures to supervise clinical trials and ensure that clinical trials are carried out according to protocol.

**Original data verification:** This study requires clinical inspectors authorized by Xi 'an Libang Pharmaceutical Co., Ltd. to directly check the original data for data verification.

The data on the patient's case report form or eCRF and the data on their original medical records are checked.

**Inspection and inspection:** representatives of Xi 'an Libang Pharmaceutical Co., LTD., regulatory department, ethics committee may inspect or inspect the research center, central laboratory and data management and statistics unit.

### **Personnel training:**

The principal investigator will maintain a record of the study training of all study participants (doctors, nurses, and others). The principal investigator will ensure that all such personnel have been properly trained in relation to the study and that any information relevant to conducting the study has been passed on to the relevant personnel.

### **Data collection and processing:**

The clinical trial investigator or clinical study Coordinator (CRC) should complete the case report form or eCRF accurately, timely, completely, and in a standardized manner according to the case Report Form or eCRF completion guidelines. The completed case report form or eCRF must be signed and dated by the investigator.

Researchers must maintain research records and data, including electronic source data and electronic documents. Each data point must be supported by original documentation in the research center. Any records or documents used as the original information (i.e. the subject's original medical documents) shall be kept securely for the sponsor's inspection and inspection by supervisory authorities.

**Subject Confidentiality:**

All records relating to the identity of the subject will be kept confidential and will not be made public to the extent permitted by relevant laws and/or regulations. The name of the subject will not be provided to the sponsor.

Only subject numbers and initials will be recorded on the medical report form. If a subject's name or other identifying information appears in any other document (e.g. pathology report), this information must be withheld before a copy of the document is provided to the sponsor. Research reports stored by computer must comply with local data protection laws. If the results of the study are published, the individual identities of the subjects will remain confidential. The investigator will maintain a list to verify the subject's identity.

**Subject compliance:**

In the recruitment selection stage, detailing the purpose of this experiment, experiment with drugs, research approach, the basic situation of the dosing process, the dosage regimen (such as dosage, dosing method, etc.), frequency and the process of clinical observation, biological samples, to test the potential risk, compensation and compensation, etc., make the subjects were informed, voluntary, increase medication compliance;

Before administration, carefully check the subject number, dose and order of administration;

During drug administration, the status of subjects should be closely observed, the feelings of subjects should be communicated at any time, and the subcutaneous injection operation should be carefully controlled.

After the administration, the changes of subjects' reactions and administration sites should be carefully observed, and appropriate medical measures should be taken if necessary.

Follow up will be conducted in strict accordance with the protocol to confirm the safety of the subjects.

